**Figure 2 f2:**
[figure not shown]
Flowchart for the win ratio according to the hierarchy of the
primary outcome.

The WR is calculated as the ratio of the total number of “wins” between the
intervention and control groups, and a WR > 1.0 indicates a better
outcome in the intervention group. The 95% confidence intervals (95%CI) for
the WR will be calculated by bootstrapping based on 10,000 samples, and
95%CI not including the unit (1.0) will be considered statistically
significant.

Secondary binary outcomes will be analyzed using a Bayesian hierarchical
logistic regression model. The model will include the study group as a
predictor and will be adjusted for study site, age, clinical suspicion of
sepsis, use of vasopressors, and mechanical ventilation at randomization. A
neutral prior of moderate strength^(29)^ and normal distribution, centered at an odds ratio
(OR) of 1.0 and a standard deviation of 0.35, corresponding to a 95%
probability that the effect (OR) is within the 0.5 - 2.0 range, will be
used. Superiority of the dapagliflozin group over the control group will be
determined if the posterior distribution of the adjusted odds ratio (aOR)
being less than 1.0 [Pr (aOR < 1.0)] is more than 95%. The results will
be presented as the posterior distribution of the aOR (in log scale), a 95%
credible interval, and the probability of the aOR being less than 1.0.

Intensive care unit-free days, hospital-free days, vasopressor-free days,
mechanical ventilation-free days, and KRT-free days will also be analyzed
using a Bayesian hierarchical ordinal model, using the same covariates from
the binary outcomes model. Frequentist analysis exploratory analysis for
secondary outcomes will also be performed, and no p values will be
presented. Binary outcomes will be analyzed thorough a logistic regression
model, with the same covariates as the Bayesian models, and data will be
presented as aOR, crude OR, and corresponding 95%CI. Treatment differences
in free day outcomes will be calculated using the Hodges‒Lehmann method and
presented as the difference in days and 95%CI.

All primary, secondary and safety analyses will follow the intention-to-treat
principle. A sensitivity safety analysis will also be conducted in all
participants who received at least one dose of dapagliflozin (safety
population). Full details of all planned analyses are provided in version
1.0 of the Statistical Analysis Plan (Supplementary Material). All analyses
will be performed using R software (R Project for Statistical
Computing).

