#### Secondary outcomes

Secondary endpoints are hospital mortality, initiation of KRT, ICU-free days,
hospital-free days, vasopressor-free days, mechanical ventilation-free days,
and KRT-free days up to 28 days after randomization, censored at hospital
discharge. To be deemed vasopressorand mechanical ventilation-free, a cutoff
of 6 hours or less in an entire calendar day will be used.

Intensive care unit-free days, hospital-free days, vasopressor-free days,
mechanical ventilation-free days, and KRT-free days endpoints are defined as
the number of calendar days alive and free from each component, measured on
an ordinal scale from 0 to 29, with higher values indicating a better
outcome. A value of 0 will be assigned to participants who die prior to
hospital discharge. Participants who are discharged prior to Day 28 will be
assumed to be free of the endpoint through Day 28.

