#### Power and sample size

We estimated that a sample size of 500 participants would provide at least
85% power to detect a win ratio and corresponding 95%CI above 1. This
calculation was made based on the following assumptions: (1) a 2% absolute
reduction in hospital mortality from 30 to 28% with dapagliflozin; (2) a 3%
absolute reduction in initiation of KRT from 10 to 7% with dapagliflozin;
and (3) a mean reduction in ICU LOS of 0.5 days with dapagliflozin. The
estimation was obtained after performing 10,000 simulations in samples of
500 participants using these assumptions and 95% confidence intervals
obtained by bootstrapping. Figure 3
displays the results of the obtained lower boundaries of the 95% confidence
intervals of the win ratio values from these simulations.

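### For KRT-free days the planned Hodges-Lehmann difference will read 0 days (95% CI 0 to 0) under essentially any benefit and all but extreme harm

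*Protocol article*

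**What the plan says.** Under Secondary outcomes, the protocol article scores five free-day endpoints (ICU, hospital, vasopressor, mechanical ventilation, KRT) on "an ordinal scale from 0 to 29, with higher values indicating a better" outcome. In-hospital death takes the lowest score: "A value of 0 will be assigned to participants who die prior to" hospital discharge. Participants discharged before Day 28 are "assumed to be free of the endpoint through Day 28".

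Under Planned Statistical Analysis, the free-day endpoints are analysed "using a Bayesian hierarchical ordinal model, using the same covariates from" the binary model. An exploratory frequentist analysis without p values is added. In it, treatment differences "in free day outcomes will be calculated using the" Hodges-Lehmann method and "presented as the difference in days and 95%CI". The estimator is stated for all five endpoints alike. The Subgroup analysis section repeats the exploratory frequentist analysis within each subgroup.

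**The concern.** The Hodges-Lehmann estimate summarises a treatment effect well when one arm's distribution is roughly a shifted copy of the other's. KRT-free days are not like that. Almost everyone is either at 0 (died) or at the top of the scale (survived without KRT), and treatment acts by moving people from one spike to the other. A median of pairwise differences hardly responds to such movement while tied pairs hold the middle of the distribution.

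The outcome would be an interval of zero width. A clinical reader takes 0 days (95% CI 0 to 0) as precise evidence of no effect, when it follows from the scoring rule and would appear under a large benefit or a substantial harm. Because no p values are shown, the estimate and its interval are the whole frequentist comparison that the article describes for this endpoint.

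**Working it through.** **Inputs from the article.** Hospital mortality 30% control, 28% dapagliflozin; KRT initiation 10% and 7% (Power and sample size); 500 participants randomised 1:1, so 250 per arm; scoring as above. The article states no operating figure for the Hodges-Lehmann analysis, so there is none to reproduce.

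**Step 1. Position of the confidence limits.** There are 250 × 250 = 62,500 differences D (dapagliflozin minus control). The rank-based 95% limits lie 1.96 × √(250 × 250 × 501 / 12) = 3,166 ranks either side of the median, and 3,166 / 62,500 = 0.051. They are therefore the 44.9th and 55.1th percentiles of D. The estimate is 0 if P(D>0) and P(D<0) are both below 0.5. The interval is 0 to 0 if both are below about 0.449.

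**Step 2. KRT-free days at the planned effect, KRT independent of death.**

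| Score | Dapagliflozin | Control |
|---|---|---|
| 0 (died) | 0.28 | 0.30 |
| between (survived, had KRT) | 0.72 × 0.07 = 0.0504 | 0.70 × 0.10 = 0.07 |
| maximum (survived, no KRT) | 0.72 × 0.93 = 0.6696 | 0.70 × 0.90 = 0.63 |

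- Ties: 0.28 × 0.30 + 0.6696 × 0.63 = 0.084 + 0.422 = 0.506.
- P(D>0): 0.6696 × 0.37 + 0.0504 × 0.30 + ½ × 0.0504 × 0.07 = 0.265.
- P(D<0): 0.63 × 0.3304 + 0.07 × 0.28 + ½ × 0.0504 × 0.07 = 0.230.

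The zeros run from about the 23rd to the 74th percentile, so the estimate and both limits lie well inside them.

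**Step 3. Other overlaps of KRT and death.** If all KRT occurs in survivors, the shares at the maximum are 0.65 and 0.60, and ties are 0.65 × 0.60 + 0.084 = 47.4%. If all KRT occurs in those who die, they are 0.72 and 0.70, and ties are 0.72 × 0.70 + 0.084 = 58.8%.

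**Step 4. Any benefit.** D can be positive only if the control participant is below the maximum. In expectation P(D>0) is therefore at most 1 − 0.60 = 0.40, 1 − 0.63 = 0.37 or 1 − 0.70 = 0.30 under the three overlaps. All are below 0.449, however effective the drug is.

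**Step 5. Harm.** Take KRT at 10% in both arms, independent of death. With 50% mortality on dapagliflozin, P(D<0) = 0.63 × 0.55 + 0.07 × 0.50 + ½ × 0.05 × 0.07 = 0.383. With 60% it is 0.63 × 0.64 + 0.07 × 0.60 + ½ × 0.04 × 0.07 = 0.447, which only just reaches the cut.

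**Step 6. Simulation of KRT-free days** (100-300 trials per scenario, KRT duration assumed).

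| Dapagliflozin arm | Estimate 0 | CI 0 to 0 | Mean difference |
|---|---|---|---|
| mortality 28%, KRT 7% (planned) | 100% | 100% | +0.7 to +0.9 day |
| mortality 15%, KRT 3% | 100% | 100% | +4.7 to +4.8 days |
| no deaths, no KRT | 100% | 98-100% | about +9 days |
| mortality 40%, KRT 15% | 100% | 100% | about −3 days |
| mortality 50% | 100% | at least 91% | about −5.7 days |
| mortality 60% | 87% | 23% | – |

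**Step 7. Ventilation- and vasopressor-free days.** The result depends on the share of survivors who never need the support. The article does not give it, so a range is shown (assumed mean/SD of support 4/3 or 7/6 days among those who need it).

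| Share never needing support | Planned mortality, 0.5 day less support: estimate 0 | Mortality 15%, 2 days less support: estimate 0 | CI 0 to 0 in the latter |
|---|---|---|---|
| 20% | 96-97% | 0-3% | 0% |
| 40% | 99-100% | 9-28% | 0% |
| 60% | 100% | 94-98% | 40-43% |
| 80% | 100% | 100% | 99-100% |

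The bound of Step 4 becomes 1 − 0.70 × share. It falls below 0.449 only when the share exceeds 0.551 / 0.70 = 0.79. At 60% the estimate stays at 0 for the effects tested, but not for every conceivable effect.

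**Step 8. ICU-free and hospital-free days** (assumed stay of survivors, mean/SD 5/3, 8/6 or 10/8 days in the ICU; 14/8 or 18/9 days in hospital).

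- Planned mortality and a stay 0.5 day shorter: the estimate is 0 in 93-95% of trials (ICU) and 96-99% (hospital). For ICU-free days the usual interval is 0 to 1, and it is 0 to 0 in only 19-32%.
- Mortality 20% and a stay 2 days shorter: the median estimate is 2 days for ICU-free days (0 in 0-7% of trials) and 1.5-2 days for hospital-free days (0 in 6-22%).

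**The case against.** Four points can be made for the plan.

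- The mechanism cannot apply to all five endpoints. Everyone starts in an ICU with an expected stay of at least 48 hours, so survivors spread over the scale for ICU-free and hospital-free days. This stands. A reader might infer that Hodges-Lehmann gives 0 days for every free-day endpoint whatever dapagliflozin does. Step 8 shows that this is not so: a usual reading of 0 at the planned effect reflects a small effect on a scale of whole days, not an estimator that cannot move.
- For ventilation and vasopressors the article gives no support rates, and both are entry criteria, so the share never needing support may be low. This stands too, and is why those two endpoints are only conditional here.
- The analysis carries little weight. It is introduced as "Frequentist analysis exploratory analysis for" secondary outcomes, the ordinal model is the main analysis and uses the ordering, and hospital mortality and KRT initiation have their own odds ratios and form the top two tiers of the primary outcome. A large mortality effect could not go unseen. This stands and sets the severity. It does not make a predetermined zero-width interval worth reporting.
- Full analysis details are deferred to an SAP that is not at hand and may hold descriptive displays by arm. It would therefore be wrong to infer that the trial will have no other summary in days. The estimator itself, however, is fixed in the article and is not an omitted detail.

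**Conclusion.** The point holds for KRT-free days. At the article's own rates 47-59% of between-arm pairs tie exactly, and the Hodges-Lehmann result will be 0 days (95% CI 0 to 0) for essentially any benefit and for all but extreme harm (mortality near 60% on dapagliflozin against 30% on control). The tie fractions and the bound under benefit need only the article's planning rates and scoring rule; the mean differences in days also rest on an assumed KRT duration.

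For ventilation- and vasopressor-free days it holds only if most survivors, about 60% or more, never need the support. That share is an assumption.

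It does not hold for ICU-free and hospital-free days, where the estimate moves by 1-2 days under larger effects. Severity is minor: one exploratory summary is affected, and no decision rests on it.

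**What to change.** For KRT-, ventilation- and vasopressor-free days, report the difference in mean free days with a bootstrap 95% CI, resampling participants within arm with 10,000 samples as already planned for the primary outcome. This can replace the Hodges-Lehmann estimate or stand beside it, and the same change should carry over to the subgroup analyses. Hodges-Lehmann may stay for ICU-free and hospital-free days.

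The cost is one sentence in the analysis text and a few lines of R. The drawback is that a mean difference treats an ordinal scale with death at 0 as numeric, so a death counts as only one day worse than a score of 1. It should therefore be read as a companion to the ordinal model and the mortality and KRT odds ratios.

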#### Subgroup analysis

For the primary and secondary outcomes, the following relevant subgroup
analyses were planned: clinical suspicion of sepsis at randomization
(yes/no), diabetes mellitus (yes/no), serum creatinine at enrollment (<
1.5mg/dL, 1.5 - 3.0mg/dL, and > 3.0mg/dL), cardiovascular reason for ICU
admission (yes/no), and age (< 65 and ≥ 65 years). Stratified WR
analysis will be performed for each subgroup stratum. The 95%CIs will be
calculated by bootstrapping 10,000 samples for each analysis, and 95%CIs not
including the unit (WR = 1.0) will be considered statistically significant.
We will also perform additional analysis for the secondary outcomes within
each subgroup using the same Bayesian models and exploratory frequentist
analysis.

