### Interim analysis and Data and Safety Monitoring Board

The DSMB regularly reviews unblinded patient-level data during the study to
ensure participant safety. The first safety analysis occurred on March 27, 2023,
after 100 participants were enrolled. An interim analysis will occur when half
of the sample size (n = 250) has been enrolled and followed for at least 14
days. For this specific analysis, trial recruitment will be halted for four
weeks and will resume only after the DSMB deliberation. Another safety analysis
is planned to occur after 375 participants are enrolled. The sole purpose of the
interim analysis is to assess safety, and the trial will not be halted for
benefit or futility. The frequency of safety interim analysis might be changed
if deemed appropriate by the DSMB members.

At the interim analysis, the DSMB will use a Bayesian framework (simple logistic
regression) to assess the posterior probability distribution for harm (OR >
1.0) for hospital mortality and initiation of KRT. If this probability is
greater than 80%, the DSMB will recommend stopping the trial. Harm will also be
assessed in two key subgroups: participants with hypotension or acute kidney
injury at randomization. If the probability of harm is greater than 80% for
either subgroup, the DSMB will recommend excluding them from the trial.

Additional interim analyses may be convened at the discretion of any DSMB member
if new scientific data or concerns arise during the study, especially regarding
the ongoing SGLT2i arms of the ACTIV-4A (NCT04505774) and RECOVERY (NCT04381936)
platform trials. Based on the interpretation and quality of the data, the number
of events, and other factors, the DSMB may recommend modifications to the
protocol (e.g., changes to inclusion/exclusion criteria), suspension, or
termination of the trial, and advise the Steering Committee. However, all final
decisions regarding trial conduct will be at the discretion of the Steering
Committee.

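### Each of 11 subgroup strata is called statistically significant on its own 95% CI; this does not test effect differences and gives a false signal in about 29–33% of null trials

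*Protocol article*

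**What the plan says.** The protocol article, under Subgroup analysis, names five factors for the primary and secondary outcomes: "clinical suspicion of sepsis at randomization", "diabetes mellitus (yes/no"), serum creatinine in three bands, cardiovascular reason for admission, and age split at 65 years. The creatinine bands and the factor after them appear as "1.5mg/dL, 1.5 - 3.0mg/dL, and > 3.0mg/dL), cardiovascular reason for ICU".

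The unit of analysis is the stratum: a stratified WR "analysis will be performed for each subgroup stratum". The intervals are to be "calculated by bootstrapping 10,000 samples for each analysis, and 95%CIs not" "including the unit (WR = 1.0) will be considered statistically significant" (one continuous sentence in the article). So a stratum counts as significant when its own 95% CI excludes 1.0.

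For the other endpoints the section adds: "We will also perform additional analysis for the secondary outcomes within" each subgroup, using the same Bayesian models plus an exploratory frequentist analysis. The word exploratory is attached only to frequentist analyses of secondary outcomes, here and under Planned Statistical Analysis. It is not attached to the primary-outcome subgroup WRs. Planned Statistical Analysis refers the reader to SAP version 1.0 for full details.

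**The concern.** Two separate problems follow from the stated rule.

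1. **Wrong comparison.** A stratum CI that excludes 1.0 is evidence of an effect in that stratum. It says nothing about whether the effect differs from that in the other stratum of the same factor, which is the usual purpose of subgroups by sepsis, diabetes, creatinine, admission reason or age. One stratum can be significant and its neighbour not when the two WRs are equal, simply because the strata differ in size or by chance.

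2. **Repeated 5% tests.** The rule grants the words statistically significant up to 11 times at an unadjusted two-sided 5%. With no true effect, a sizeable share of trials would carry at least one such label, for benefit or for harm. The temptation to promote one is greatest when the overall result is not significant. The article presents the trial as the first of this drug class in general ICU patients and as informing future trials, so a chance stratum could influence who is studied next.

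**Working it through.** **The plan's own figure.** The article states no subgroup error rate, so there is none to reproduce. Its stated power of at least 85% does not enter this check.

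**Inputs from the article.** Strata: 2 (sepsis) + 2 (diabetes) + 3 (creatinine) + 2 (cardiovascular admission) + 2 (age) = 11. Error rate per stratum: 5% two-sided, from the 95% CI. Sample: 500, allocated 1:1.

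**Inputs assumed.** The article gives neither stratum sizes nor correlations between factors, so both were varied. The four sets below list the proportions in the order sepsis; diabetes; creatinine; cardiovascular; age.

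- A: 50/50; 70/30; 60/25/15; 70/30; 50/50
- B: equal strata throughout
- C: 60/40; 75/25; 70/20/10; 80/20; 50/50
- D: 80/20; 85/15; 80/15/5; 85/15; 60/40

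Correlation between factors was set at 0, 0.3 and 0.6.

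**Step 1, independent strata.** 1 − 0.95^11 = 1 − 0.569 = 43.1%. This overstates the risk, because the same 500 participants reappear in every factor.

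**Step 2, overlapping strata.** 40,000 null trials per setting, with a stratum counted as significant when |z| > 1.96. The last column uses one between-stratum test per factor at 5%.

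| Set | Correlation | Any significant stratum | Any favouring dapagliflozin | Any, when overall result not significant | Any of 5 between-stratum tests |
|---|---|---|---|---|---|
| A | 0 / 0.3 / 0.6 | 32.5 / 32.1 / 29.6% | 16.9 / 16.6 / 15.3% | 29.0 / 28.7 / 26.0% | 22.5 / 22.1 / 20.0% |
| B | 0 / 0.3 / 0.6 | 32.3 / 31.7 / 29.3% | 16.7 / 16.5 / 15.1% | 28.8 / 28.3 / 25.8% | 22.6 / 22.1 / 19.7% |
| C | 0 / 0.3 / 0.6 | 32.5 / 31.8 / 30.2% | 16.8 / 16.4 / 15.6% | 28.9 / 28.3 / 26.7% | 22.4 / 21.7 / 20.4% |
| D | 0 / 0.3 / 0.6 | 32.8 / 31.9 / 30.2% | 17.2 / 16.5 / 15.8% | 29.2 / 28.5 / 26.6% | 22.6 / 21.8 / 20.5% |

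Under the null with 1:1 allocation, harm mirrors benefit; a direct count gave about 17% for harm.

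**Step 3, check with the actual endpoint.** Win-ratio trials were simulated with 250 per arm and the article's hierarchy, a pair who both die being a tie. Both arms had 30% mortality and 10% KRT. ICU stay was log-normal with assumed mean 8 and SD 6, in whole days up to 28. The large-sample standard error of log WR replaced the bootstrap, and unrelated factors were assumed. Any significant stratum: 32.9% (set A), 30.7% (B) and 31.3% (D), with 1,500 trials each (simulation error about ±1.2 points, one standard error). This agrees with Step 2.

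**Step 4, what a between-stratum test leaves.** Five tests at 5%: 1 − 0.95^5 = 22.6% if independent, and about 20–23% in the table. At 1% each the bound is 5 × 1% = 5% (1 − 0.99^5 = 4.9% if independent).

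**The case against.** The strongest reply is that this is a condensed article and that SAP version 1.0, which is not shown, may contain an interaction test and a rule for multiplicity. That is right as far as it goes. A reader might infer that the trial has no between-stratum comparison at all; the documents support only that the article states none. The point survives because the article does more than stay silent: it fixes a significance rule for each stratum, and that sentence would need correction whatever the SAP adds.

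A reader might also attribute the 29–33% to the missing between-stratum comparison. It comes from 11 unadjusted 5% tests. Replacing them with one comparison per factor corrects what is being tested but lowers the false-signal rate only to about 20–23%.

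It is tempting to quantify how often the rule would show an effect here but not there when the true effect is uniform. The article gives no mean, SD or distribution for ICU stay, and such figures swing widely with that assumption. A significant stratum under a true uniform effect is also not a false positive. No figure is offered.

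The DSMB's interim review has harm "assessed in two key subgroups: participants with hypotension or acute kidney" injury at randomization, and neither group is in the final subgroup list. This could be read as an inconsistency. Those groups serve interim safety monitoring, nothing in the article requires the lists to match, and adding factors would add comparisons.

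Finally, the article does not say that a significant stratum supports a claim of effect modification. For secondary outcomes the frequentist part is labelled exploratory, no p values are to be presented, and the Bayesian models use a neutral prior. The error figures here therefore concern the primary outcome only.

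**Conclusion.** The point holds. The rule tests the wrong thing for a subgroup question and, applied to 11 strata without adjustment or an exploratory label, gives at least one false significant stratum in about 29–33% of null trials (43% if the strata were independent). About half of these are for harm. Where the overall result is not significant, the rate is still about 26–29%.

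The range rests on assumed stratum sizes and correlations but moves little across them. It also assumes that each bootstrap interval has close to its nominal 5% error. The primary analysis is not affected; what is unprotected is the interpretation of the subgroups. This should be changed before the results are analysed.

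**What to change.** 1. Delete the sentence that calls a stratum significant when its own CI excludes 1.0. Show stratum WRs with 95% CIs descriptively.
2. For each two-level factor, report the ratio of the two WRs (the difference in log WR) with a bootstrap 95% CI. For the three creatinine strata, use a joint test of equal WRs.
3. In the secondary-outcome models, use a treatment-by-subgroup term rather than relying on separate fits within strata.
4. Label all subgroup results exploratory, or adjust across the five factors: for example 99% CIs for the ratios and the 1% level for the creatinine test, which keeps the chance of any false signal at or below 5%.
5. If the SAP already has a between-stratum test, align the two documents and remove the within-stratum rule wherever it appears.

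The cost is analysis wording and a small change to the bootstrap code, with no new data. The price is wider intervals if the adjusted option is taken, and no stratum-level significance claims.
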